## Abstract

**Background:**

Ensuring effective and long-term contraception in the immediate postpartum period is an effective strategy for reducing unplanned pregnancies. In the meantime, the intrauterine device (IUD) is an excellent option. The aim of our study was to evaluate the best way to insert post-placental IUDs in the immediate postpartum period. Discomfort during insertion, expulsion rate, uterine perforation rate, and proper positioning 40–60 days postpartum will be analyzed.

**Methods:**

Randomized, controlled, open clinical trial. The study group will be composed of women between 18 and 43 years old who are admitted for vaginal birth at the Women’s Hospital of the State University of Campinas and who wish to use the IUD as a contraceptive method. The sample will be randomized into two insertion groups: manual and forceps. To calculate the sample size, the method of comparing the proportion between 2 groups was used, setting the level of significance alpha at 5% (alpha=0.05) and the power of the sample at 80% (beta=0.20). Based on the results, it was estimated that a sample of *n*=186 women (*n*=93 with manual insertion and *n*=93 with forceps) would be representative for comparison of expulsion between the 2 groups. All participants will undergo a postpartum consultation 40–60 days after birth with transvaginal ultrasound to assess the proper placement of the IUD.

**Discussion:**

Insertion of an IUD in the immediate postpartum period has been considered a good option to increase coverage and access to contraception, and its benefit outweighs the inconvenience of a higher expulsion rate.

**Trial registration:**

This study was approved by the Ethics and Research Commission of UNICAMP (CAAE: 50497321.4.0000.5404) and the Brazilian Registry of Clinical Trials (REBEC) (number RBR-4j62jv6). This is the first version of the study protocol approved on 11/12/2021 prior to the start of participant recruitment.

**Supplementary Information:**

The online version contains supplementary material available at 10.1186/s13063-022-07041-x.

## Background

The first 12 months after birth is a period when a subsequent pregnancy is at increased maternal/infant risk [1]. The importance of postpartum reproductive planning is already clearly documented, with a reduction in the risk of miscarriage, low weight at birth, neonatal and maternal death, premature delivery, and anemia [2, 3]. Reproductive planning could prevent more than 30% of maternal deaths and 10% of child deaths if the interpartum interval was at least 2 years [4].

After childbirth, 40% of women who need contraception do not have access to contraceptive methods [5]. This is aggravated in times of crisis, such as the COVID-19 pandemic, in which access to health services was restricted and reproductive planning programs were reduced, despite their essential character [6, 7].

A study of nearly 15,000 women showed that 95% of those who wanted contraception underwent insertion of an intrauterine device (IUD) during hospitalization, while only 45% of women did so after discharge [8]. For 40% of women, sexual activity returns before 6 weeks postpartum and without the use of contraceptives [9]. Thus, delaying the start of effective contraception can favor a new unplanned pregnancy in a short period of time [10].

Compared with definitive sterilization, the use of the IUD is simpler, less expensive and immediately reversible. Insertion of the IUD after delivery can avoid the discomfort related to interval insertion (≥ 4 weeks postpartum) reported by some women who undergo the procedure without anesthesia, sometimes requiring cervical dilation.

However, immediate insertion, that is, that performed within 10 min after delivery of the placenta (post-placental IUD), can also have disadvantages. The risk of expulsion is usually greater [10]. Three systematic reviews have shown that IUD insertion in the immediate postpartum period is safe and effective when compared to later insertions (more than 10 min to 48–72 h or after 6–8 weeks of delivery) [11–13]. Comparing insertion during hospitalization for delivery, immediate insertions are associated with lower expulsion rates than later insertions (e.g., 2 to 72 h after placental delivery) [11, 12]. The systematic review carried out by the Cochrane group included 9 studies. Comparing immediate insertion and after 6–8 weeks, a higher expulsion rate was found in the group with immediate insertion, but with the same proportion of women using the device at 6 months [11].

Insertion of the copper IUD after vaginal delivery can be done manually by moving the device to the uterine fundus with your fingertips or using long ring-tipped forceps, such as the modified Kelly forceps. There is also a long inserter specially developed for this purpose. However, it is not widely available on services.

The aim of our study is to evaluate the best way to insert the IUD in the immediate postpartum period: manually or with the use of modified Kelly placental forceps. Discomfort during insertion, expulsion rate, uterine perforation rate, and proper positioning 40–60 days postpartum will be analyzed.

## Methods/design

### Study type

Randomized, controlled, open clinical trial.

### Setting

The study will be conducted at the Woman’s Hospital, University of Campinas Medical School, Campinas, Brazil. The facility is a tertiary referral public hospital that offers treatment and is a referral for approximately 40 municipalities, covering a population of more than five million inhabitants.

### Outcomes

#### Primary

Expulsion rate

#### Secondary

Infection rate

Perforation rate

Discomfort during insertion

Ultrasound positioning of the IUD

Side effects (increased bleeding and dysmenorrhea)

### Inclusion and exclusion criteria

The study will include women between 18 and 43 years old, with a single pregnancy, who have vaginal birth, who wish to use the IUD as a contraceptive method, and who do not have contraindications, namely, uterine malformation; uterine fibroids that deform the cavity; diagnosis or suspicion of ovular infection; diagnosis or suspicion of infection elsewhere; active sexually transmitted infection; and severe anemia (hemoglobin less than 8.0 mg/dl during antenatal care). Women who, after signing the consent form and randomization, wish to withdraw from the study for any reason, present with fever during labor or delivery, rupture of amniotic membranes for more than 24 h, manual extraction of the placenta, postpartum hemorrhage or uterine atony will be withdrawn from the study.

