### Intervention

The possibilities of postpartum contraception and the benefits of starting a method before hospital discharge will be discussed during antenatal consultations or on admission for childbirth for women with external antenatal care. Women who want the copper IUD as a contraceptive method will be informed about its durability, side effects, advantages, and disadvantages of its insertion after placental delivery. Women who wish to participate in the study will be randomly assigned to one of the groups (forceps or manual insertion), through a computer-generated numerical allocation list. Randomization will be kept confidential in a sealed envelope until the time of insertion. In the immediate postpartum period, the copper IUD will be inserted according to the result of the randomization. Only members of the research group, with specific training, will be able to insert the IUD after signing the consent form by the patient. Study participants will remain unsure to which group they were allocated.

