### Follow-up

Participants will be followed on the same service. Between 40 and 60 days postpartum, they should return for postpartum consultation and pelvic ultrasound to assess the IUD and cut the wires (see Table 1). In cases where the woman has an IUD in situ and without visualization of the threads in the cervical canal, the follow-up will be exclusive with pelvic ultrasound. For women who have expelled IUDs or who have IUDs in the cervical canal, a new device of the woman’s preference will be offered. In cases where the woman is not satisfied with IUD, another contraceptive method will be offered and made available.

**Table 1 Tab1:** Procedures and techniques

	Study period					
	Enrollment		Allocation	Post allocation		
	Prenatal consultations	Admission for childbirth	Randomization	Immediately after randomization	In the labor and delivery room following delivery	Postpartum consultations and pelvic ultrasound
**Timepoint**	**T−2**	**T−1**	**T0**	**T1**	**T2**	**T3**

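### Withdrawal for hemorrhage, atony or a wish to leave is not limited to the time before the allocation envelope is opened, so the expulsion comparison can be biased

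*Protocol article*

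**What the plan says.** The withdrawal rule is in the protocol article under Inclusion and exclusion criteria. It covers "Women who, after signing the consent form and randomization, wish to withdraw from the study for any reason". It also covers fever in labor or delivery, membranes ruptured for over 24 h, and women with "manual extraction of the placenta, postpartum hemorrhage or uterine atony will be withdrawn from the study". The rule starts at randomisation. It has no end point and is not tied to the opening of the envelope or to insertion.

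Other sections fix the sequence around it:

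- Inclusion and exclusion criteria: the trial takes women "with a single pregnancy, who have vaginal birth, who wish to use the IUD as a contraceptive method". Vaginal birth is certain only at delivery.
- Intervention: "Randomization will be kept confidential in a sealed envelope until the time of insertion".
- Background: post-placental insertion is defined as taking place within 10 minutes of placental delivery.
- Study type: "Randomized, controlled, open clinical trial". The Intervention section adds that participants are not to know their group.
- Outcomes: the primary outcome is "Expulsion rate", which Table 1 assesses at the 40 to 60 day visit.
- Follow-up, Table 1: both insertion techniques are marked at T1, headed "Immediately after randomization". This comes before T2, the column for the delivery room after birth, where pain during insertion is marked.

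**The concern.** A randomised comparison is protected as long as decisions about who stays in the study cannot be influenced by the arm. That protection ends when the envelope is opened. With insertion so soon after the placenta, hemorrhage or atony can be recognised when the device is already in place and the operator knows the technique. A woman may also wish to leave because insertion was painful. She need not know her group for this to differ by arm. The Discussion itself expects forceps to be more comfortable for women without labor analgesia and manual insertion to give fewer expulsions.

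If women leave for reasons linked both to technique and to the chance of expulsion, those who remain are no longer comparable. The rule speaks of withdrawal from the study, and expulsion is assessed weeks later. If follow-up stops, no later analysis plan can recover the missing outcomes.

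**Working it through.** **Step 1. Which withdrawals can follow a known allocation?**

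| Reason | Can it arise after the envelope is opened? |
|---|---|
| Birth not vaginal | No |
| Fever in labor or delivery | No |
| Membranes ruptured over 24 h | No |
| Manual placental extraction | No |
| Postpartum hemorrhage, uterine atony | Before or after |
| Wish to leave | Before or after |

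Only the last two rows can bias the comparison, and only for withdrawals after opening.

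**Step 2. The plan's own figure.** The Sample size section gives 186 women (93 per arm), alpha 5% and power 80%. The expulsion rates behind it are not printed, so 186 can be neither confirmed nor refuted. With p̄ the mean of p1 and p2, the usual two-sided formula is

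n per arm = [1.96·√(2p̄(1−p̄)) + 0.842·√(p1(1−p1)+p2(1−p2))]² / (p2−p1)²

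Solved backwards for 93, it is met by, for example, 5% vs 18.1%, 10% vs 25.7% or 20% vs 38.6%. For lower rates of 5 to 20%, the trial is therefore sized for differences of about 13 to 19 points.

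**Step 3. Bias as a risk difference.** Let p be the true rate in an arm, w the share withdrawn after opening, k the rate in women kept, and D the excess risk of withdrawn over kept women. Then p = (1−w)k + w(k+D), so k = p − wD. If D is the same in both arms, the bias in the risk difference is (difference in w) × D. The document gives neither quantity. With assumed values:

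- 0.05 × 0.20 = 0.010
- 0.05 × 0.30 = 0.015
- 0.10 × 0.20 = 0.020
- 0.10 × 0.30 = 0.030

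**Step 4. The same check with a risk ratio.** If withdrawn women are RR times as likely to expel as those kept, then k = p/(1 − w + w·RR). The true rate is set equal in both arms, and RR = 3 is assumed:

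| True rate | Withdrawn, arm A vs B | Seen in A vs B | False difference | Type I error |
|---|---|---|---|---|
| 10% | 5% vs 15% | 9.1% vs 7.7% | 1.4 points | 6.2% |
| 20% | 2% vs 10% | 19.2% vs 16.7% | 2.6 points | 7.3% |
| 20% | 5% vs 15% | 18.2% vs 15.4% | 2.8 points | 7.7% |
| 30% | 5% vs 15% | 27.3% vs 23.1% | 4.2 points | 9.6% |

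For the third row, the numbers kept are 93 × 0.95 = 88.35 and 93 × 0.85 = 79.05. The standard error is √(0.1818·0.8182/88.35 + 0.1538·0.8462/79.05) = 0.0577 and the shift is 0.0280/0.0577 = 0.485. The rejection rate is 1 − Φ(1.96 − 0.485) + Φ(−1.96 − 0.485) ≈ 0.077. With RR = 1, or with equal withdrawal and the same RR in both arms, the false difference is zero and the type I error is 5.0%.

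**Step 5. Lost outcomes and numbers.** If expulsion status is unknown for 9 of 93 women per arm (about 10%), best-case and worst-case limits on the risk difference are 2 × 9/93 = 0.194 wide. That is about 19 points, the upper end of the differences in Step 2. If 186 is the number randomised and 10% per arm are lost, about 83 per arm remain and power falls from 80% to about 75%. The same loss of power follows from exclusions before opening, which cause no bias.

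**Step 6. Table 1 against the text.** A device placed after the placenta cannot be placed in a column that precedes delivery, and pain during insertion cannot be scored in a later period than the insertion. The table and the text need to be reconciled. This inconsistency is separate and adds nothing to the bias argument.

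**The case against.** Several points on the other side are sound.

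- A reader might infer that randomising before eligibility is complete is itself a source of bias. The documents do not support that. The envelope stays sealed until insertion, so exclusions for events in labor or at delivery are made without knowledge of the arm. They cost numbers, not validity.
- A reader might also infer that the plan definitely drops women after insertion. It does not say so. The rule stands among the eligibility criteria, most of its clinical items precede insertion, and both technique descriptions have the uterus palpated for tone before the device is placed. The fault is a missing time limit, and a pre-insertion reading is possible.
- Withdrawal from the study does not define an analysis set. Analysis populations are commonly left to a statistical analysis plan, so silence on them is no fault. What can be criticised is the withdrawal rule as written, because it can end follow-up before the primary outcome is assessed.
- A participant may leave at any time. That cannot be restricted, and listing it is no error.
- Participants are not told their group. This weakens the idea that they leave because they know the technique, but not the idea that they leave because of pain.
- The size rests wholly on assumed inputs, and 1 to 3 points is small beside differences of about 13 to 19 points.

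What remains is that hemorrhage and atony can follow a known allocation, the rule as written then removes the woman, and nothing in the document says that she stays in follow-up.

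**Conclusion.** The point holds in a limited form. The rule permits withdrawal from the study after the allocation is known, for reasons that may be related both to technique and to expulsion. This can bias the primary comparison. It does not show that the comparison will be biased, or in which direction.

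Bias requires three things together: withdrawals after opening, an imbalance between arms in their number or kind, and a different expulsion risk in the women withdrawn. The document gives no figure for any of these. Under the assumed inputs the bias is about 1 to 3 percentage points, or up to 4.2 points in the least favourable row shown (true rate 30%, RR 3). It is zero if the withdrawals are unrelated to expulsion, or if they are equal in share and kind between arms. The case for acting is that the repair is cheap and must be made while follow-up can still be kept, not that a large bias has been shown.

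**What to change.** Amend the protocol as follows. The changes concern study follow-up and analysis only, not clinical management.

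1. Check every inclusion and withdrawal criterion after placental delivery and before the envelope is opened, and record the check in one line of the envelope log.
2. Restrict clinical exclusions from the study to events recorded before opening, and report them with reasons.
3. Follow every woman whose envelope is opened to the 40 to 60 day visit and analyse her in her allocated group. Record hemorrhage, atony or fever noted after opening as events, not as grounds for leaving the study.
4. Let a woman who withdraws consent contribute data up to that point, and add a sensitivity analysis for missing expulsion status.
5. For the 30 women already included (Trial status), note whether any withdrawal came before or after opening.
6. Separately, reconcile the timing of insertion in Table 1 with the post-placental timing in the text.

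The cost is a short amendment and the log entry. The envelope is already opened at insertion, so no extra participants, staff or procedures are needed.

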### Intervention

The possibilities of postpartum contraception and the benefits of starting a method before hospital discharge will be discussed during antenatal consultations or on admission for childbirth for women with external antenatal care. Women who want the copper IUD as a contraceptive method will be informed about its durability, side effects, advantages, and disadvantages of its insertion after placental delivery. Women who wish to participate in the study will be randomly assigned to one of the groups (forceps or manual insertion), through a computer-generated numerical allocation list. Randomization will be kept confidential in a sealed envelope until the time of insertion. In the immediate postpartum period, the copper IUD will be inserted according to the result of the randomization. Only members of the research group, with specific training, will be able to insert the IUD after signing the consent form by the patient. Study participants will remain unsure to which group they were allocated.

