**Assessments:**						
**Pain or discomfort during insertion**					x	
**Expulsion**						x
**Uterine perforation**						x
**Proper positioning**						x

Orientation, insertion, and removal of misplaced IUDs will be performed by a group of trained resident physicians and supervised by an experienced chief. To guarantee the standardization and constant review of the technique, periodic training offered by the researchers is planned. After insertion, the professional responsible for the procedure is recorded so that we can later correlate whether the expulsion and/or mispositioning was influenced by the experience of the professional who performed the procedure.

The insertion technique will be briefly described below. For insertion with the forceps, the patient must be in a lithotomy position with the feet or knees supported. Asepsis of the vulva, vagina, and cervix will be performed with aqueous chlorhexidine solution. The uterus will be palpated to assess the fundus and tone. The evaluator must wear sterile gloves and must gently insert the vaginal speculum. The anterior labrum of the cervix should be clamped with a Collin clamp. The physician’s nondominant hand rested on the uterine fundus. The IUD should be secured using modified Kelly forceps (see Fig. 1). The physician's nondominant hand rested on the uterine fundus, and the IUD was gently placed through the cervix using forceps. The forceps must then be opened and withdrawn completely from the side. The clamp from the labrum of the cervix and the vaginal speculum should both then be removed.

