**Fig. 1 Fig1:**
[figure not shown]
Modified Kelly forceps

For manual insertion, the patient must be in a lithotomy position with the feet or knees supported. Asepsis of the vulva, vagina, and cervix will be performed with an aqueous chlorhexidine solution. The uterus will be palpated to assess the fundus and tone. The evaluator must wear sterile gloves and must gently insert the device by holding it between the second and third fingers of the hand. The hand must be closed in order to completely protect the IUD so that it does not touch the vaginal walls (see Fig. 2). The physician’s nondominant hand rested on the uterine fundus, and the IUD was gently placed through the cervix and into the fundus.

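### The trial is labelled open, yet participants are said not to know their group although the two insertions differ physically; no masking of the 40–60 day ultrasound reading is stated either

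*Protocol article*

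**What the plan says.** The Methods part of the abstract and the Study type section both call the trial open: "Randomized, controlled, open clinical trial".

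The Intervention section makes two separate statements about knowledge of allocation. The first concerns concealment: "Randomization will be kept confidential in a sealed envelope until the time of insertion". The second comes three sentences later, after insertion has been described, and concerns the women: "Study participants will remain unsure to which group they were allocated".

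The insertion techniques are described under Follow-up. In the forceps arm the operator "must gently insert the vaginal speculum", and then "The anterior labrum of the cervix should be clamped with a Collin clamp", before the device is placed with modified Kelly forceps. In the manual arm the operator "must gently insert the device by holding it between the second and third fingers of the hand", with the hand closed around the device. No speculum, clamp or forceps is described for that arm.

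Discomfort during insertion is a listed secondary outcome, and Table 1 places it in the delivery room. Table 1 places expulsion (the primary outcome), perforation and positioning at the postpartum consultation with pelvic ultrasound. The scan is done in the hospital's Diagnostic Imaging Department. The machine, probe, frequency and settings are given; whether the reader knows the arm is not.

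**The concern.** There are two parts, of unequal strength.

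The first is a conflict in the printed text. A trial in which the women do not know their group is not open with respect to the women, and nothing in the described procedures would keep them from knowing. Discomfort is the woman's own report and so the outcome most sensitive to this. If the Intervention sentence stands, discomfort could later be read as participant-blind.

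The second part concerns the ultrasound. The article gives no measurable criterion for a badly placed device, so some judgement enters the call. The call has consequences: devices judged badly placed in the cavity, or found in the endocervical canal, are removed. Removals would presumably enter the Kaplan–Meier analysis of continuation and discontinuation. A reader who knows the arm could therefore influence both ultrasound positioning and discontinuation. The Discussion states a direction in advance: the authors expect manual insertion to give better placement and fewer expulsions, and forceps to be more comfortable for women without labour analgesia. When the investigators hold such expectations, the reading of position is worth protecting.

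**Working it through.** The point rests on the text. The arithmetic at the end only gives a sense of scale.

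**1. Is the Intervention sentence just allocation concealment?** No. Concealment has its own sentence, the sealed envelope, and ends when the device is inserted. The sentence about participants has no time limit and follows the description of insertion. Its natural meaning is that the women do not learn their group.

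**2. Do the procedures allow that?**

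| Step (Follow-up) | Forceps arm | Manual arm |
|---|---|---|
| Position, antisepsis, palpation of the fundus | yes | yes |
| Vaginal speculum | yes | not described |
| Clamp on the cervix | yes | not described |
| How the device is carried in | Kelly forceps | closed hand |
| Removal of clamp and speculum | yes | not described |
| Screen, sham step or other means of masking | not described | not described |

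The arms share the preparation and differ in everything after it. Masking is stated but has no mechanism.

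**3. Which outcomes could an unmasked reading at 40–60 days affect?**

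- Ultrasound positioning: directly, because it is a judgement.
- Discontinuation: through the removals that follow that judgement.
- Expulsion: less, because a missing device leaves little to interpret.
- Discomfort, infection and side effects: not through the scan. They come from the woman, the examination or the questionnaire.

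**4. Scale, on assumed values.** The only relevant figure in the article is the sample size of 186, or 93 per group. The two expulsion rates behind it are not printed, so it cannot be reproduced here, and masking the reader would not change it. Suppose all 93 women per arm are assessed and a rate p, which the documents do not give, applies in both arms. The 95% confidence half-width for the difference is 1.96 × √(2p(1 − p)/93):

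- p = 0.10: 1.96 × √(0.18/93) = 0.086
- p = 0.15: 1.96 × √(0.255/93) = 0.103
- p = 0.20: 1.96 × √(0.32/93) = 0.115

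If knowledge of the arm changed the position call for 5% of women in one arm (0.05 × 93 ≈ 5 women), the difference would move by 5 points. That is 0.05/0.086 = 58%, 0.05/0.103 = 49% or 0.05/0.115 = 43% of the half-width. The 5% is an assumption, and nothing in the documents suggests that a shift of this or any other size would occur.

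**The case against.** The strongest reply is that only the wording conflict is established. The article never says that the ultrasound reader knows the arm. It condenses a fuller protocol, which may say what appears on the scan request. This stands: an unmasked reading is an inference from the open label and from silence. The ultrasound part is therefore a recommendation to protect the reading, and it does not allege that the reading is unmasked.

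A reader might infer several stronger things that the documents do not support:

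- *Every woman will know her arm.* The procedures make this plausible, most of all without analgesia. But insertion follows directly on delivery, and the Discussion implies that some women have analgesia. What can be said is that the claimed masking has no support.
- *The assessors share the authors' expectation.* The Discussion reports what the authors expect. Nothing attributes this to the imaging department.
- *The inserters classify the outcome.* The article says that "Orientation, insertion, and removal of misplaced IUDs will be performed by a group of trained resident physicians". Removal comes after position has been judged, and the postpartum visit is run by a physician, nurse and psychologist.
- *A device in the canal counts as a partial expulsion.* Follow-up lists expelled devices and devices in the cervical canal as separate cases, and no sentence merges them for the primary outcome.
- *The ultrasound decides the outcomes generally.* It bears on position and partly on expulsion and perforation, and not on the other outcomes.

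It could also be said that the sentence about participants refers only to the time before insertion. On that reading it repeats the envelope sentence, and should still be reworded because it does not say so.

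**Conclusion.** The point holds in two parts. First, with high confidence, the open label and the statement about participants conflict, and the described procedures do not support participant masking. Discomfort should be treated as an unblinded self-report. This rests only on printed text.

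Second, with moderate confidence, the position reading should be protected. No masking is stated, the label is open, the call involves judgement and leads to removal, and the investigators have declared which arm they expect to do better. Ultrasound positioning and discontinuation are the outcomes exposed; the primary outcome is exposed to a lesser extent. The size of any bias is unknown. The comparison of 5 points with a half-width of about 10 points shows scale under assumed values and is not an estimate.

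This should be corrected, but it does not threaten the sample size or the basic design.

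**What to change.** 1. Reword the Intervention sentence to agree with the open label: allocation is concealed until the envelope is opened at insertion, and neither the operator nor the woman is masked after that. If the full protocol does contain a means of keeping women unaware, describe it and qualify the open label instead.
2. Describe discomfort during insertion as an unblinded self-report, in the plan and in the results.
3. Leave the arm off the ultrasound request. Have the Diagnostic Imaging Department record device presence and location before anyone involved in the reading sees the allocation, and state that this reading is the one analysed.
4. Have the reader note whether the arm was known, so that imperfect masking can be reported.

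The cost is a change to the request form and a few sentences. A separate department already does the scan, so no extra assessor or visit appears necessary, although the documents do not cost this. Masking may be imperfect if the arm is visible in the clinical record. Clinical care and the sample size do not change. Trial status reports 30 of the planned 186 women included, so 186 − 30 = 156 were still to come. Scans already read should be reported as done before the change.
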